### Candidate Intervention Components and Intervention Delivery

The three candidate intervention components to be evaluated were selected according to the two-process model of sleep-wake regulation (Borbely et al., 2016). To further minimize burden, only the sleep restriction and stimulus control components of CBT-I will be evaluated while sleep hygiene education, cognitive restructuring, and relaxation therapy will not, as sleep restriction and stimulus control have been identified as primary mechanisms of CBT-I efficacy among adherent patients (Morin et al., 2006).

#### Sleep Restriction

Sleep restriction involves limiting one’s opportunity for sleep to the amount of time reported sleeping on an average night plus 30 min. For this study, wake time will be determined by asking participants to identify the earliest time they need to awaken on any given day based on their individual lifestyles. The prescribed bedtime will then be identified by working backward from this wake time. The initial sleep opportunity window will be informed by 7 days of sleep diaries completed immediately prior to beginning the intervention. This window will then be adjusted weekly based on participants’ sleep efficiency (i.e., ratio of time asleep to time in bed at night), calculated from weekly sleep diaries, as is the gold standard recommendation (Spielman et al., 1987).

#### Stimulus Control

Based on classical and operant conditioning, stimulus control aims to disassociate non-sleep behaviors from the bedroom and reinforce the association of the bedroom with sleep-related stimuli (e.g., bed). Instructions include not going to bed until sleepy, getting out of bed if unable to fall asleep or fall back to sleep within approximately 20 min, avoiding behaviors other than sleep and sexual activity in the bedroom, waking up at the same time each day, and avoiding daytime naps (Bootzin et al., 1991).

#### Systematic Bright Light Exposure

Bright light will be systematically delivered by wearable Re-Timer™ glasses. The Re-Timer™ glasses are a small (7.9″×5.5″×2.2″), lightweight (2.64 oz.) device that delivers green-blue light from below to replicate the natural pathway of light to the eyes. Participants will be instructed to wear the glasses on the highest setting for 30 min every morning during the intervention period, initiating this time within 30 min of awakening and completing light exposure prior to noon. Re-Timer™ glasses can be worn over traditional eyeglasses as long as the eyeglasses do not have photochromatic or tinted lenses.

#### Intervention Delivery

Prior to the initiation of the intervention period, research staff will provide an intervention orientation to participants. This orientation, which will last approximately 30–60 min, will be completed either in-person or over video conference, and will include general sleep education as well as an explanation of the intervention components the participant will receive and the rationale behind them. After this orientation, participants will implement their assigned intervention components at home daily for 6 weeks.

The candidate intervention components will be administered *via* weekly emails. All participants will monitor their sleep by completing a daily sleep diary for the duration of the 6-week intervention period. All participants will also receive a weekly email from the study team with a reminder to complete and return the sleep diary. Sleep diaries will be returned electronically. For participants receiving stimulus control, the weekly email will also contain a reminder of the stimulus control instructions. For participants receiving systematic bright light exposure, the weekly email will also contain a reminder of how to use the Re-Timer™ glasses. For participants receiving sleep restriction, the weekly email will also contain a reminder of the sleep restriction instructions and the prescribed sleep schedule for the coming week, which will be determined by a licensed clinical psychologist with specialized training in behavioral sleep intervention ([name]) based on the prior week’s sleep diary. Participants receiving more than one candidate intervention component will receive a single weekly email containing the information relevant to all components being delivered. The study team will be available to participants throughout the intervention period to answer questions, troubleshoot, and provide support as needed.

### Study Design

This two-part study is guided by the MOST framework. Participants in Part 1 will not be randomized, but rather will receive all three candidate intervention components simultaneously. It is well established that greater adherence predicts behavioral sleep intervention efficacy; however, knowledge of how best to increase adherence is limited (Matthews et al., 2012, 2013; Agnew et al., 2021). Therefore, upon completion of the intervention in Part 1, individual semi-structured interviews will be conducted with participants and analyzed to identify barriers to and facilitators of adherence to the three candidate intervention components. Results will inform the design and delivery of the components in Part 2 to enhance adherence. Subsequently, in Part 2, a full factorial experiment will be completed that involves eight experimental conditions (Table 1). It is important to note that this study is not an eight-arm RCT and the purpose is not to compare outcomes across each of the eight conditions directly. Rather, each main effect and interaction estimate will use data from participants in all of the experimental conditions. For example, the main effect of sleep restriction will be estimated by comparing the mean for the 40 participants in conditions 1 through 4 to the mean for the 40 participants in conditions 5 through 8 in Table 1. A detailed explanation of how factorial study designs maintain power has been previously published (Collins et al., 2009).

**TABLE 1 T1:** Experimental conditions.

Experimental condition	Sleep restriction	Stimulus control	Bright light
1	Yes	Yes	Yes
2	Yes	Yes	No
3	Yes	No	Yes
4	Yes	No	No
5	No	Yes	Yes
6	No	Yes	No
7	No	No	Yes
8	No	No	No

### Hypotheses

We hypothesize that gynecologic cancer survivors will be able to engage with each of the three candidate intervention components and that each component will be deemed acceptable. We further hypothesize that the optimal combination of intervention components will yield stronger effects for diminishing sleep disturbance, improving HRQOL, and reducing symptom burden than each individual component.

## Data Collection and Measures

### Data Collection

Data to be collected include sociodemographic information, medical information, patient-reported outcome measures, qualitative patient feedback, urine samples, and objective sleep information recorded by actigraphy. Throughout the study, the REDCap (Harris et al., 2009) data collection platform will be used to capture and store participant data. This platform is optimized for secure research data collection and storage and allows for HIPPA-compliant export and analysis. Data will be entered into REDCap either directly by participants or by the research team. All study assessments will be completed in-person or remotely *via* videoconference.

Across both Part 1 and Part 2 of the study, the screening questionnaire will be administered by telephone to determine eligibility. Eligible and interested participants will then provide informed consent before completing a baseline assessment where they will provide sociodemographic and medical information and complete questionnaires related to their sleep, HRQOL, and symptom burden. Participants will also collect urine the night before this baseline assessment, wear a wrist actigraph, and complete sleep diaries for the 7 days leading up to the assessment. Immediately after completing the 6-week intervention period, participants will complete a follow-up assessment that mirrors the baseline plus an additional measure of acceptability. In addition to the baseline and post-intervention assessments, participants in Part 1 will complete a semi-structured interview and accompanying survey within 2 weeks of completing the intervention to provide information about barriers to and facilitators of protocol adherence. In contrast, participants in Part 2 will complete an additional follow-up assessment 3 months after completing the intervention that mirrors the baseline and post-intervention assessments to measure longitudinal intervention effects.

### Measures

#### Feasibility and Acceptability

In both Part 1 and Part 2, study feasibility will be assessed according to established procedures (Bowen et al., 2009), including documenting the number of eligible participants, participant willingness to be enrolled, attrition, reported reasons for withdrawing, and self-reported protocol adherence.

Acceptability of the candidate intervention components will be assessed with items from the Functional Assessment of Chronic Illness Therapy – Treatment Satisfaction – General scale (FACIT-TS-G) (Peipert et al., 2014), which will be administered at the post-intervention assessment only. The FACIT-TS-G includes eight items that utilize Likert-type response scales, were developed as stand-alone single items, and are scored individually. Higher item scores indicate greater acceptability.

#### Covariates

##### Sociodemographic and Medical Information

Sociodemographic and medical information will be gathered through participant self-report and medical chart review at screening, baseline, post-intervention, and 3-month follow-up. Sociodemographic data will include age, education, income, racial background, ethnicity, employment status, and relationship status. Medical data will include information about exclusionary and comorbid medical conditions, prescription medication use, and cancer-related information (e.g., time since diagnosis, stage at diagnosis, treatment history). Participants will also complete the Self-Administered Comorbidity Questionnaire (Sangha et al., 2003).

##### Sleep Apnea Risk

The Berlin questionnaire (Netzer et al., 1999) will assess risk for sleep apnea at baseline. This screener consists of nine items reflecting known clinical features of sleep apnea and yields scores in three categories related to the risk of having sleep apnea. Participants are classified as High Risk or Low Risk based on their responses to individual items and their overall scores in the symptom categories.

##### Pain

An 11-item numerical rating scale, ranging from 0 (*No pain*) to 10 (*Worst imaginable pain*), will evaluate pain intensity (Ferreira-Valente et al., 2011) at baseline, post-intervention, and 3-month follow-up. The numerical rating scale is one of the most commonly used measures of pain intensity and has been shown to be responsive to pain (Ferreira-Valente et al., 2011).

##### Treatment Expectancy

Following the baseline assessment and orientation session and prior to the start of the 6-week intervention period, participants will complete the Credibility/Expectancy Questionnaire (Devilly and Borkovec, 2000). This six-item measure was developed for clinical studies to measure treatment expectancy and rationale credibility. It yields two subscale scores reflecting affectively based expectancy and cognitively based credibility.

#### Primary Outcomes

##### Objectively Measured Sleep

The Actiwatch Spectrum Plus (Mini Mitter/Phillips/Respironics) will be used to objectively measure sleep/wake activity at baseline, post-intervention, and 3-month follow-up. In addition to sleep/wake activity, the Actiwatch Spectrum Plus records information about amount and duration of ambient white light luminance in units of lux. Participants will wear the device, which is similar in size to a watch, on the non-dominant wrist for 7 consecutive days immediately prior to each assessment. Actiwatch Spectrum Plus data will be scored and analyzed with Actiware Sleep v6.1.2 (Phillips-Respironics, Mini Mitter, Bend, OR, United States) to calculate sleep outcomes, such as total sleep time, percent sleep, total wake time, number and duration of nighttime awakenings, sleep mid-point, and number and duration of daytime naps (defined as a minimum of 10 consecutive min of inactivity). These data will also be used to calculate circadian activity rhythms (Marler et al., 2006) and the sleep regularity index (Phillips et al., 2017), which are indicators of circadian rhythm robustness. Participants will be instructed to press the event marker on the Actiwatch when initiating sleep effort at the start of the main sleep period, when discontinuing sleep effort upon final awakening, and when taking daytime naps. When wearing the Actiwatch, participants will also complete an actigraphy log in which they will record instances of and reasons for Actiwatch removal, which will be used to inform editing of the actigraphy data (Ancoli-Israel et al., 2015).

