
A leading theory of sleep-wake regulation is the two-process model (Borbely et al., 2016), which posits that sleep timing and intensity depend on the interaction of a homeostatic process and a circadian process, which function independently. According to this model, the homeostatic process reflects the body’s attempts to maintain balance, in that more time spent awake leads to increased pressure to fall asleep (Deboer, 2018). The circadian process, a pacemaker managed by the suprachiasmatic nucleus of the hypothalamus, determines one’s daily rhythm for sleep and wake, leading to increased sleepiness at certain times of the day and increased alertness at others (Deboer, 2018). Thus, sleep-wake cycles and circadian rhythms separately influence sleep (Borbely et al., 2016). Sleep restriction and stimulus control, the two core components of CBT-I, both target the homeostatic process. Conversely, systematic bright light exposure targets the circadian process. Therefore, combining sleep restriction, stimulus control, and bright light may have additive or even interactive effects. One known study is currently exploring this hypothesis (Bean et al., 2020); however, it is doing so exclusively among patients undergoing chemotherapy for breast cancer. Thus, the applicability of results to cancer survivors who have completed primary treatment will be unclear. Additionally, this known study is adding systematic bright light exposure to CBT-I as a packaged intervention, thus increasing the burden associated with this already challenging treatment. To maximize benefit from the available evidence-based treatments, studies are needed that can determine what combination of behavioral sleep intervention components yields the most effective intervention while also maximizing adherence to optimize impact.

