#### Part 2: Intervention Optimization

For Part 2, we will use benchmarks of 80% recruitment (i.e., 80% of eligible survivors) and 80% retention to demonstrate feasibility. We will use a benchmark of 60% protocol adherence for each candidate intervention component, based on prior studies of CBT-I and bright light in cancer survivors (Berger et al., 2003; Ancoli-Israel et al., 2012). Descriptive statistics will be applied to the FACIT-TS-G items to examine acceptability.

To identify the optimal combination of candidate intervention components, longitudinal mixed effects models will be fit to the data with primary and secondary outcomes evaluated in separate models. All study time points will be included in these models, and fixed effects will include time (a nominal variable with three levels, which will be entered as two indicator variables), each candidate intervention component, and two-way interactions among components. The effect of a component at post-intervention and 3-month follow-up will be assessed based on that component’s interaction with time. Candidate intervention components will be defined using effect coding (absence: −1, presence: +1) so effects remain uncorrelated (Kugler et al., 2012). Models will also adjust for hypothesized covariates as outlined above, as well as demographic and baseline clinical characteristics found to significantly differ across conditions. Further analyses will evaluate if the presence of multiple candidate intervention components has a greater effect on each outcome than single components. To do this, an additional variable will be created to indicate the number of components to which a participant was exposed (0, 1, 2, 3). This variable will be included as a fixed effect in these models, along with its interaction with time.

In addition to optimizing the intervention, we will also explore the potential mediating role of circadian markers (i.e., aMT6s, circadian activity rhythms, sleep regularity) on the effects of candidate intervention components. The potential mediating role of sleep disturbance on the relationships of intervention components to HRQOL and symptom burden will also be evaluated. Given the exploratory nature of this analysis, interpretation will focus on effect sizes rather than statistical significance.

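### Two actigraphy markers read as circadian mediators score the regularity that sleep restriction and stimulus control prescribe, so an indirect effect through them can reflect schedule adherence alone

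*Protocol article*

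**What the plan says.** The section Objectively Measured Sleep takes two kinds of quantity from one wrist record. The record is scored "to calculate sleep outcomes, such as total sleep time, percent sleep, total wake time", awakenings and naps. The text then adds: "These data will also be used to calculate circadian activity rhythms", together with the sleep regularity index, "which are indicators of circadian rhythm robustness".

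Part 2: Intervention Optimization plans to explore the "potential mediating role of circadian markers (i.e., aMT6s, circadian activity rhythms, sleep regularity) on the effects of candidate intervention components". The sentence excepts no component, gives none of the three markers precedence, and names no outcome or time lag. The analysis is declared exploratory and is to be read on effect sizes.

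Two components prescribe timing. The Stimulus Control instructions include "waking up at the same time each day, and avoiding daytime naps". Under Sleep Restriction, the participant names a wake time, and then "The prescribed bedtime will then be identified by working backward from this wake time". Intervention Delivery adds a schedule sent each week.

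Actigraphy covers the 7 days before each assessment. Data Collection fixes the second assessment: "Immediately after completing the 6-week intervention period, participants will complete a follow-up assessment that mirrors the baseline".

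The introduction states the mechanism the design rests on: sleep restriction and stimulus control "both target the homeostatic process. Conversely, systematic bright light exposure targets the circadian process".

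**The concern.** For these two components the mediator is partly the instruction itself. A participant who keeps the prescribed bed and wake times, or rises at a fixed hour and stops napping, will score as more regular whether or not her circadian rhythm has changed. Called a circadian marker, that score becomes evidence of a circadian mechanism.

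What is at stake is the mechanistic conclusion. The protocol assigns these two components to the homeostatic process and bright light to the circadian one. Two of its three circadian markers can show a path for exactly the components not meant to work that way. Reading effect sizes instead of p-values gives no protection, because the adherence contribution sits in the effect size.

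A second, conditional issue is that the index and the objective sleep outcomes come from the same epochs. If they are paired within one week, fewer wake epochs can raise the index by arithmetic.

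**Working it through.** The plan states no figure for the mediation analysis, so there is nothing to reproduce. The check is whether the markers can move with no circadian change, and by how much under stated assumptions.

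**1. Timing.** The 7 days before an assessment held directly after week 6 are the last intervention week. As written, the schedule is still assigned while the marker is recorded.

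**2. Hand calculation for the regularity index.** Assumed form: index = 200 × P(same sleep/wake state 24 h apart) − 100. If bedtime and wake time each vary independently from night to night with SD s minutes (normal), the mean absolute difference between two nights is 2s/√π = 1.128s for each edge. With two edges the mismatch is 2.257s minutes per 1,440, so the index loses about 200 × 2.257s/1,440 = 0.313s points. Reducing s to an assumed 15 min gives:
- from 30 min: 0.313 × 15 = 4.7 points
- from 45 min: 0.313 × 30 = 9.4 points
- from 60 min: 0.313 × 45 = 14.1 points

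This ignores wake within the night.

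**3. First simulation.** 500 records per group, 7 days of 1-minute states, no circadian process. Assumed: median timing SD 30, 45 or 60 min unprescribed and 15 min prescribed; mean 60 min wake after sleep onset. The indirect effect is the product of coefficients on total wake time from the same record.

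| Scenario | Index, SD 30 / 45 / 60 | Indirect effect (min) |
|---|---|---|
| Prescribed schedule | 74.8→78.8 / 71.1→79.2 / 66.7→78.8 | −10.4 / −14.6 / −16.2 |
| Same, 60% adherence | 74.1→77.2 / 70.3→75.2 / 67.0→74.5 | −7.0 / −5.5 / −7.1 |
| Fixed wake time, few naps | 74.1→79.7 / 70.4→77.8 / 66.2→75.6 | −13.2 / −12.4 / −8.9 |
| Fewer wake minutes only | 74.1→78.4 / 69.8→74.0 / 66.2→69.6 | −5.7 / −3.4 / −1.4 |

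The prescribed-schedule rises are 4.0, 8.1 and 12.1 points (0.6 to 1.3 SD), in line with step 2. In the first three rows the true difference in wake time is between −0.4 and +2.6 min.

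The last row isolates shared epochs, with the schedule unchanged. The total effects are −21.2, −23.3 and −23.3 min, so the share attributed to the marker is 5.7/21.2 = 27%, 3.4/23.3 = 15% and 1.4/23.3 = 6%.

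**4. Second simulation.** 200 trials of N = 80 in the 2×2×2 design, no circadian process. Assumed: bedtime SD 40–90 min and wake-time SD 40–80 min, cut to 40% when prescribed; naps cut to 30% under stimulus control. The index changes by 0.0 points with neither component, 16.7 with sleep restriction, 5.7 with stimulus control and 19.1 with both. Standardized indirect effects on percent sleep (a × b, components coded −1/+1):

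| Marker | Sleep restriction | Stimulus control |
|---|---|---|
| Regularity index | 0.708 × 0.634 = 0.45 | 0.191 × 0.634 = 0.12 |
| Cosinor amplitude | 0.435 × 0.279 = 0.12 | 0.288 × 0.279 = 0.08 |
| Cosinor R² | 0.468 × 0.334 = 0.16 | 0.331 × 0.334 = 0.11 |

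The path from bright light to each marker is about 0. The cosinor measures stand in for activity rhythms, whose exact computation is not shown. Sleep restriction here also shortens time in bed, so its 16.7 points and 0.45 mix steadier timing with fewer wake epochs.

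**5. What this does not cover.** Both simulations use a same-week actigraphic outcome. Neither gives an indirect effect on a PROMIS score. For PROMIS outcomes only the first link, from assignment to marker, has been shown.

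**The case against.** The strongest reply is that the mediation sentence names no outcome, time point or model. Same-record pairing is possible but not stated. The PROMIS sleep scales are also primary outcomes, a 3-month record exists, and an article may leave pairing to the full plan. This stands, so the shared-epoch point is conditional.

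The sizes rest on assumed inputs, and the two simulations disagree on stimulus control: level with sleep restriction in one, about a third of it (5.7 against 16.7 points) in the other. Stimulus control also leaves bedtime open, since participants go to bed only when sleepy. The large indirect effects in the first simulation occur where the total effect is near zero, so the main model would show nothing to explain. These points also stand.

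A reader might infer that any observed path through these markers is an artefact. The documents do not support that. The introduction allows for interaction between the two processes, and a regular schedule might strengthen a rhythm. A model with no circadian process shows only that the path can arise without one. The two markers cannot separate the two explanations, and that is enough to bar the circadian reading for these components.

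Finally, the analysis is exploratory and aMT6s offers a check outside the activity record. Both are true, but the plan gives aMT6s no precedence.

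**Conclusion.** The concern holds as a possibility that the plan itself creates by fixing the markers, their circadian label and the recording week. For sleep restriction and stimulus control, an indirect effect through sleep regularity or activity rhythms can come from schedule adherence alone.

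The size cannot be determined from the documents. Under the assumptions shown, a prescribed schedule raises the index by 3 to 12 points across 60% and full adherence in one simulation, and by 16.7 points in the other, where time in bed also shortens. The effect is likely larger for the index than for activity rhythms (0.45 against 0.12 to 0.16 for sleep restriction). For stimulus control it is uncertain and may be modest.

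It would be wrong to conclude that spurious mediation will appear, or that the choice of components is compromised. Component effects are estimated in separate mixed models that do not use these markers as mediators. The bright-light path to the markers is not directly affected, because no fixed wake time is prescribed with it. The change should be made, but its reach is limited to what the trial may say about mechanism.

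**What to change.** In Objectively Measured Sleep and in Part 2: Intervention Optimization:

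- Describe the sleep regularity index and circadian activity rhythms as rest-activity (behavioural) regularity.
- For sleep restriction and stimulus control, do not read an indirect effect through these two markers as circadian mediation. Rest circadian claims for these components on aMT6s.
- Keep the two markers as circadian mediators for bright light only. Put assignment to the other two components and the baseline marker in both the mediator and the outcome model, since those components can move both marker and outcome. Adjusting for assignment does not remove differences in adherence within a component, and the report should say so.
- Pair the markers with PROMIS Sleep Disturbance or with a 3-month outcome, not with an actigraphic outcome from the same 7 days. The lag removes shared epochs. It does not change what the week-6 marker measures, so it does not replace the second point.

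The cost is wording; all measurements and time points are already planned. One exploratory claim is given up. A lagged analysis uses only participants with 3-month data: 0.80 × 80 = 64 if the plan's 80% retention benchmark is met at that visit.
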